**B: Trial Follow-up Phase**

1. **7-10 day follow-up for surgical patients**

Team members

Nurse

Driver 2, if patient fails to attend for follow up

1. Find appropriate patients according to suture removal lists from each trial.
2. Record post operative examination on new form for patient
3. Double check that this patient is from trial 2 and therefore has silk (BLACK) sutures.
4. Remove all sutures.
5. Record removal of sutures on masterlist E5
6. Give patient further instructions

Masterlist E5

| Unique identifier | Name | Date of suture removal | Eye of suture removal | Early post operative findings |
| --- | --- | --- | --- | --- |
|  |  |  |  |  |
|  |  |  |  |  |
|  |  |  |  |  |

Examination

1. Are/is there:
   1. Discharge
      1. Purulent
      2. Non-purulent
   2. Obvious granuloma (do NOT evert lid)
   3. Bleeding
   4. Early recurrence
      1. Count eyelashes and record
   5. Skin infection / cellulitis
2. Is further surgery being planned?
   1. When?
   2. Where?

Procedure if early recurrence is identified

Either:

1. Operate immediately, if suitably trained surgeon is present
2. Refer to Bahir Dar for urgent re-op
3. Refer to another local surgical campaign, if there is capacity and a suitably trained surgeon.

Failure to present at 7-10 follow up

1. Is this due to:
   1. Death
   2. Travelled
   3. Unknown
2. Driver and suture removal nurse to take all possible steps to find patient or arrange for their presentation as soon as possible for suture removal.

Late complications

If patient re-presents between the 7-10 day follow up and the 3 month follow up, record reason and presence/absence of any of the above complications and follow procedure above.

1. **6 month follow up**

Team

Field Co-ordinator with SR assistance

Driver 1

Assistants

Aims

Full examination and photography

Swabs

1. **One year follow up**

Team

SR

Field co-ordinator

Assistants

Driver 1

Aims

Full examination and photography

Questionnaire

Visual acuity

Swabs

1. **18 month follow up**

Team

Field co-ordinator with SR assistance

Driver 1

Assistants

Aims

Full examination and photography

Swabs

1. **Two year follow up**

Team

SR

Field co-ordinator

Assistants

Driver 1

Aims

Full examination and photography

Swabs

**Typical project day protocol (diagram 1)**

Triage patient

Identify suitable areas for different parts of recruitment process

Lecture and info sheet to all patients

Not trachoma

Trachoma

Emergency

Non-emergency

Arrangements for urgent attendance at local eye unit or acute treatment in field if required and possible.

Instructions for attendance at local eye unit and referral letter if required

Not suitable for study, i.e. exclusion criteria

Suitable for study 1

Allocate unique patient identifier

Suitable for study 2

Allocate unique patient identifier

Treat in field as per clinical need and patient choice, including surgery if required

Consent

Consent

Questionnaire

Questionnaire

Measure VA, height, weight

Measure VA, height, weight

Examine patient

Examine patient

Photograph

Photograph

Randomise

Randomise

Surgery

Surgery

Epilation training

Post-op instructions

Post-op instructions

Post-op instructions

Nurse 1, assistants 1,2 + SR

Nurse 1

SR/EO/Nurse 1,2,3 or 4

Nurse 1,2,3 or 4

Nurse 2,3 or 4

Assistants 1+2

SR, Nurse 1, Assistnant 5

Assistant 6

Nurse 2,3,4 assistant 7

Assistant 8

Assistant 6

Nurse 2,3,4 assistant 7

SR

Nurses 2,3,4

Nurses 2,3,4

Assistants 3+4

Nurses 2,3,4

**Appendix A – The project team**

**The team**

SR (Research Fellow)

Co-ordination

Examination and clinical photography

Field Co-ordinator (Nurse 1)

Trained in:

1. Examination and will then conduct 6 and 18 month follow up.
2. Triage

Nurse 2, 3 and 4 (surgery nurses)

Trachoma surgeons. Technique validated and standardised by [name]/[name]

Nurse 5

Suture removal.

Assistants 1 and 2 (consent field workers)

Trained in:

1. Project explanation/presentation
2. Consent taking
3. Questionnaire administration

Assistants 3 and 4 (Vital statistics field workers)

Trained in measuring

1. Logmar visual acuity
2. Height
3. Weight

Assistant 5 (examination field worker)

Trained in assisting SR with:

1. Examination
2. Photography
3. Microbiological swabbing

Assistant 6 (randomisation field worker)

Trained in how randomisation/masking etc

Assistant 7 (surgical assistant)

Trained in assisting nurses with surgery

Assistant 8 (epilation field worker)

Trained in teaching epilation

Driver 1

Project team driver

Driver 2

Project team driver; suture removal team driver

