**(b) Epilation training**

Team Members

Assistant 8 (epilation field worker)

Procedure

*A. If patient and suitable relative both present at surgical camp*

1. Take patient and relative to designated epilation training area.
2. Re-explain purpose of trial
3. Explain need for:
   1. Good quality epilation
   2. Regularity of epilation
4. Test near vision of relative.
5. Show forceps to relative and ask if they have epilated previously.
6. Warn of hazards of forceps:
   1. Corneal trauma
   2. Breaking lashes to leave abrasive stubs
   3. Remind that there is a contact number on the information sheet if difficulties do arise and give named person to contact in case of concerns.
7. Tell relative of need for good lighting and undisturbed location.
8. Observe relative epilating.
9. Check lid after epilation:
   1. If epilation fully successful (no trichiatic lashes remain): give epilation pack as per (10)
   2. If epilation partially successful (no lashes touching globe/cornea, but trichiatic lashes remain) (i.e. give advice.
   3. If epilation failed (lashes touching globe/cornea):
      1. Either: repeat full epilation training
      2. Or: ask if another more appropriate relative is available

But do NOT exclude from trial.

1. Give epilation pack:
   1. Forceps
   2. Lid diagram/diary cards in A4 plastic wallet.
   3. Pencil

*B. If patient not with suitable relative*

1. Investigate if suitable relative can be found: consider:
   1. Either: Deferring epilation training until later in the week
   2. Or: project driver to fetch relative.

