**3.10. - 3.12 Assess epilation**

- 1. Is there clinical evidence of epilation? No/yes
  2. How much epilation is there? None, <1/3rd, 1/3rd-2/3rd, >2/3rd
  3. How successful is the epilation? none, successful, <6 lashes, 6+ lashes
  4. **Photograph trichiasis (right and left)**
  5. **Assess plica semilunaris:**

Is the plica semilunaris:

a) Normal: see glossary.

b) Diseased but present. A fold of skin is present, but this is either distorted in shape or scarred down to the underlying conjunctiva.

c) Effaced: the plica semilunaris is absent.

- 1. **Assess for symblepharon (upper or lower): no/yes**

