**Studies on the Management of Trachomatous Trichiasis**

**Analytical Plan for Trial 2: Randomized controlled trial of immediate surgery vs. epilation for Minor Trichiasis**

**1. Participant flow**

*a) Eligibility, enrolment and follow-up*

The following will be shown by trial arm in a flowchart following CONSORT guidelines for non-inferiority trials (JAMA 2006: 295:1152-1160): Numbers eligible, consenting to take part, randomized, and who received the intended treatment. The numbers still in follow-up, censored, defaulting, and permanently lost-to-follow-up respectively at each visit will also be shown by arm. Reasons for declining to take part, not having surgery, or discontinuing follow-up will be summarized by arm.

*b) Censoring*

Patients in both arms will be considered as failures and immediately censored when they present with 5+ lashes in the trial eye. In addition, patients who present having had surgery (or repeat surgery) on the trial eye from other providers will be considered as failures and immediately censored.

1. **Description of baseline data**

The following characteristics of participants at baseline will be tabulated by arm:

- 1. Socio-demographic factors: age, sex, literacy, ethnic group.
  2. Behavioural factors: epilation habits, whether surgery has previously been offered, reasons for not having surgical treatment previously.
  3. Clinical status: trichiasis, entropion, inflammation, conjunctivilisation of lid margin, corneal scarring, evidence of epilation, visual acuity, symblepharon.

The distributions of these variables by treatment arm will be compared, to assess whether there is imbalance at baseline in these potential confounding factors.

1. **Primary outcome**

*a) Definition*

The primary outcome measure will be the proportion of participants with 5 or more lashes touching the eye on one or more follow-up visits. Lids with eyelash stubs which are not in contact with the eye will not be considered a treatment failure.

*b) Justification of primary outcome measure*

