Trichiasis (lashes touching the eyeball) causes visual loss through corneal opacification. The purpose of the interventions being compared in this trial is to stop eyelashes touching the eyeball. It is anticipated that some of the patients in the surgery arm of the trial may commence epilation if their surgery fails. From an ophthalmic public health perspective they are ‘successes’ if they successfully prevent eyelashes touching the globe, despite the surgery itself having not been totally successful.

Previous studies have used a cut-off of 5 or more lashes for determining treatment choices (Arch Ophth 2006; 124: 309-314). Similarly, this level has been used in national blindness control programmes (The Gambia) as an indication for surgery.

*c) Sample size*

Our sample size of 1300 trial participants would provide 90% power to detect non-inferiority, assuming 10% loss to follow-up over 2 years, a 5% failure rate in the surgery arm, and non-inferiority margin of 10%. (i.e we would conclude non-inferiority if the upper 95%CI for the observed difference in failure rates was less than 10%)

The power to detect non-inferiority under different assumptions with this sample size is shown in the table below

**Table 1:** Power for detecting non-inferiority under different assumptions with sample size of 585 per arm (1300 recruited, 10% loss to follow-up)

| **Proportion failing in surgery arm (**[figure not shown] | **Proportion failing in epilation arm (**[figure not shown] | **Difference in proportions (**µ) | **Inferiority margin (**Δ) | **Power** |
| --- | --- | --- | --- | --- |
| 2% | 6% | 4% | 8% | 93% |
| 2% | 8% | 6% | 10% | 89% |
| 3% | 6% | 3% | 8% | 98% |
| 3% | 9% | 6% | 10% | 85% |
| 4% | 8% | 4% | 8% | 82% |
| 4% | 8% | 4% | 10% | 99% |
| 4% | 9% | 5% | 10% | 94% |
| 5% | 9% | 4% | 8% | 76% |
| **5%** | **10%** | **5%** | **10%** | **90%** |
| 8% | 11% | 3% | 8% | 83% |
| 8% | 12% | 4% | 10% | 93% |

*d) Statistical analysis*

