Surgical complications such as granuloma, incomplete lid closure, inflammation from suture material and infection can occur. The clinical status of the eyelid at the suture removal (7-10 days) will be described. The risk of complications in the surgical arm of the trial will be calculated at one year and two years respectively. The risk of recurrence (defined as at least one lash touching the eyeball or clinical evidence of epilation or redo surgery) will also be estimated at each visit.

1. *Patient satisfaction*

Patients are asked the following questions on the follow up questionnaires that indicate their satisfaction with the procedure:

- 1. *Do you think your vision is worse, the same or better than before your surgery or epilation?*
  2. *Do you have eye pain?*
  3. *If you have eye pain is it worse, the same or better than before your surgery or epilation?*
  4. *Do your eyes water?*
  5. *If you had surgery, did you find it painful?*
  6. *If you have been epilating do you find it painful?*
  7. *If you had surgery and the eyelashes have returned, do you want to have further surgery?*
  8. *If you have been epilating would you prefer to have had surgery?*

1. The answers to each of these questions will be compared between the two arms of the trial at 12 months. Additionally the answers to questions (b) and (d) will be adjusted for baseline (pre-operative) response.

Footnotes

1. *Why is corneal opacification not the primary outcome measure?*

Although corneal opacification is the outcome that is responsible for blindness (rather than trichiasis which is a risk factor for this) it can not be used as a primary measure for the following reasons:

1. As few as 10% of patients will have corneal opacity at the outset of the study.
2. The rate of change of corneal opacity can be slow, and the clinical examination is not sensitive enough to detect very subtle changes
3. Corneal opacity can be caused by other insults such as infection and trauma.
4. *Why is visual acuity not the primary outcome measure*

As with corneal opacity, loss of visual acuity is the end stage process from the disease. However it can not be used as a primary outcome measure because it is affected by many other common conditions such as cataract, as well as simply by aging.

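### No step keeps the follow-up examiners unaware of arm, although the primary outcome is their own lash count at a five-lash threshold

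*Protocol*

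**What the plan says.** **Who counts.** In Appendix A the field co-ordinator is trained in "Examination and will then conduct 6 and 18 month follow up". Section B, Trial Follow-up Phase, lists "Field Co-ordinator with SR assistance" at 6 months, the equivalent at 18 months, and both people at 12 and 24 months. The same two triage, examine and photograph at recruitment.

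**What is decided.** "The primary outcome measure will be the proportion of participants with 5 or more lashes touching the eye on one or more follow-up visits". A second route to failure does not depend on the count: "patients who present having had surgery (or repeat surgery) on the trial eye from other providers will be considered as failures and immediately censored".

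**What bears on masking.**
- Appendix C has the envelope opened by the surgeon and the randomisation worker, out of the rest of the team's sight. One copy of the treatment list stays with that worker and the other goes to someone independent of the trial.
- Appendix A mentions masking in that worker's training.
- A short section restricts code-breaking for individual patients.
- Appendix G allows the DSMC to see unblinded interim data.
- The analytical plan reports a blinded pooled failure rate.

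**What can show the arm at follow-up.** Appendix B has the examiner record evidence of epilation (3.10–3.12) and a separate conjunctival scar grade after previous surgery (3.24–3.25). The epilation pack alone contains "Lid diagram/diary cards in A4 plastic wallet". The follow-up questionnaire asks, for example, "If you have been epilating would you prefer to have had surgery".

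**The concern.** Each masking provision covers the moment of allocation, a code-break, the DSMC or the pooled analysis. None says what the person counting lashes at 6, 12, 18 or 24 months may know.

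Previous eyelid surgery is an exclusion, so if the follow-up examination repeats Appendix B, a surgical scar grade will usually identify a surgery-arm eye. Counting before eversion protects the first such visit. It does not protect later visits by the same examiner, or one who can read the earlier form.

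The count is a clinical judgement, and one lash (4 or 5) can separate success from failure. In a non-inferiority comparison, under-counting in the epilation arm or over-counting in the surgery arm moves the estimate towards the claim. The authors chose their analysis population specifically to avoid bias towards non-inferiority, but specify no matching protection for outcome measurement.

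**Working it through.** **Inputs.** "Our sample size of 1300 trial participants would provide 90% power to detect non-inferiority, assuming 10% loss to follow-up over 2 years" (Sample size). Evaluable per arm: 1300 × 0.9 / 2 = 585. Margin 10%; non-inferior if the upper two-sided 95% limit is below 10%.

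**1. The plan's own figures.**
- Table 1, 5% v 10%: SE = √(0.05×0.95/585 + 0.10×0.90/585) = 0.01533. Power = Φ((0.10 − 0.05)/0.01533 − 1.96) = Φ(1.30) = 90.3% (stated 90%).
- Table 2, Wald limit = difference + 1.96 × SE. For 4.5% v 11.5% (26 v 67 failures): 7.01% + 1.96 × 1.568% = 10.08% (stated 10.1%). For 4% v 12% (23 v 70): 8.03% + 1.96 × 1.564% = 11.10% (stated 11.1%).

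**2. Recounts that turn the result non-inferior** (epilation failures scored below 5, Wald limit).

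| Surgery v epilation | Failures | Upper limit | Recounts needed | Upper limit after |
|---|---|---|---|---|
| 4.5% v 11.5% | 26 v 67 | 10.08% | 1 | 9.90% |
| 4% v 12% | 23 v 70 | 11.10% | 6 | 9.99% |
| 3% v 13% | 18 v 76 | 12.98% | 17 | below 10% |
| 2% v 14% | 12 v 82 | 15.00% | 27 | below 10% |

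Six recounts are 6/585 = 1.0% of the arm and 6/70 = 8.6% of its failures. Over-calling eight surgery eyes at 4% v 12% has the same effect.

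**3. Score test.** The analytical plan specifies exact methods, while Table 2 matches Wald limits. A score test is closer to the former: z = (observed difference − 0.10)/SE₀, with SE₀ from the maximum-likelihood rates constrained to differ by 0.10, compared with one-sided 0.025.
- 23 v 64 (six recounts): z = −1.89, p = 0.030, not met.
- 23 v 63 (seven): z = −2.00, p = 0.023, met.
- From 26 v 67, one recount gives p = 0.026 and two give p = 0.020, so two are needed.

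**4. The opposite direction.** At Table 2's 5% v 11% (29 v 64, limit 9.06%, non-inferior), over-calling six epilation eyes gives 29 v 70: difference 7.01%, limit 10.17%, no longer non-inferior.

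**5. Error rate at the margin.** True rates 5% v 15%; a fraction f of epilation failures is under-counted, so the observed epilation rate is 0.15(1 − f). Probability that the Wald rule declares non-inferiority, by summing over all pairs of binomial outcomes:

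| f (assumed) | Observed epilation rate | Declared non-inferior |
|---|---|---|
| 0 | 15.00% | 2.7% |
| 5% | 14.25% | 6.9% |
| 10% | 13.50% | 15.1% |
| 15% | 12.75% | 28.4% |

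With f = 10% and a true difference of 10 points, the figure is 14.8% to 16.1% for surgery failure rates from 2% to 8%.

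**The case against.** **Roles are separated.** Surgery, suture removal and epilation training belong to other staff, and the code-break rule suggests that masking was intended. This stands as far as it goes: the documents do not show that the examiners know the arm. But intention is not a procedure for the follow-up visit.

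**Some routes are weaker than they look.** A reader might infer that the recruitment questionnaire reveals the arm; it cannot, because it precedes randomisation. Appendix A gives questionnaires to assistants 1 and 2, and nothing says that diary cards reach the examiner. Visible epilation is no certain marker, since the plan expects some surgery patients to epilate. A reader might also infer that no safe examination order exists, but Appendix B already puts the lash count and "Photograph trichiasis (right and left" before eversion and scar grading. What remains is the scar grade and epilation record, carried forward by the same examiners or on earlier forms.

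**The size may be overstated.** A one-lash lean affects only eyes near the threshold and must recur at every visit where the eye would qualify. The documents give no lash distribution or observer agreement, and surgery elsewhere fails without any count. All this stands.

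**The 5% v 15% case implies 10% pooled failure against the reported 8%.** The gap is 0.02/√(0.10×0.90/1170) = 2.3 standard errors. However, the 8% rests on the same counts: with 15% under-counting the expected pooled rate is (5% + 12.75%)/2 = 8.9%. The inflation is also similar at other surgery failure rates.

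**It may be too late.** The analytical plan describes blinded analyses at the end of the trial, so new visit rules may no longer change conduct. That limits the remedy, not the gap in the text.

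**Conclusion.** The concern holds in a limited form. As written, nothing keeps the follow-up examiners unaware of arm, although their clinical count drives the primary outcome and their own examination records signs of treatment. Between about 4% v 12% and 4.5% v 11.5%, one to six recounts by the Wald limit (two to seven by a score test) would turn the result non-inferior. At the margin, assumed under-counting of 5% to 15% raises false non-inferiority from 2.7% to between 6.9% and 28.4%.

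The under-count fractions are assumptions. The direction is unknown: over-calling epilation failures would work against the claim. At 3% v 13% or 2% v 14%, 17 or 27 recounts would be needed, so a small lean would not matter.

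A reader might infer that the protocol is silent on masking except in one worker's training, or that the result is biased towards non-inferiority. The documents support neither: several provisions concern blinding, though none covers the follow-up count, and there is no evidence of an actual lean.

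**What to change.** In Section B, Trial Follow-up Phase, and in Appendix B, state that:

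1. the follow-up examiner has no access to masterlists E2–E5, earlier examination forms or diary cards;
2. the existing order (lash count and lid photograph, then eversion and scar grading) also applies at follow-up and comes before any question about treatment;
3. the assistants, not the examiner, give the questionnaire and collect the diaries.

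Optionally, add a sensitivity analysis in which existing staff masked to arm recount eyes near the threshold from the lid photographs. This depends on the photographs allowing globe contact to be judged, which the documents do not show; Appendix B describes photograph grading only for the cornea. If the visits are already complete, state what the examiners knew; the recount is then the only one of these measures still open.

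The cost is minor visit logistics and, if chosen, some regrading time. Masking will remain incomplete where epilation or surgical marks are visible.

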**Appendix B – Questionnaire and examination protocol and study record form**

**Patient Examination**

1. **General Examination**
   1. **Height in centimetres**
   2. **Weight in kilograms**
   3. **Determine trial eye**

Use pre-designed random eye table

- 1. **Record eye being treated**

1. **Ophthalmic Examination**
   1. **Visual Acuity:**  **EDTRS tumbling E logmar chart at 4m**

a) Best corrected

b) Pinhole vision

To calculate LogMAR visual acuity for 4m:

1. Test to lowest line on which any letter can be read. Complete whole line, even if many mistakes.

2. Take the LogMAR score for the lowest complete line read

3. Add 0.02 x n to this score, where n = the number of letters read from the non-completed line.

N.B

If chart is read at 2m: add 0.3 correction

If chart is read at 1m: add 0.6 correction

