**Secondary outcomes**

1. *Number of lashes touching the eye at each visit.*

This will include data from all time points. We expect a large proportion of individuals with no lashes touching, and will thus use a random effects zero-inflated Poisson analysis (Lee et al, Statistical Methods in Medical Research 2006:15:47-61). This model is suitable for count data with an excess of zeros, and adjusts for within-patient correlation. The model will provide a coefficient, 95%CI and p-value for the difference in log mean number of lashes in the intervention versus control arms.

1. *Lashes touching the cornea:*

The number of lashes touching just the cornea will be compared between the two arms of the trial. Lashes that only touch the peripheral eyeball (i.e. the sclera rather than the cornea), are probably not of great visual or pathological significance. This will be analysed with similar methods to that for the total number of lashes touching the eye at each visit.

1. *Entropion grade*

The effect of the intervention on the degree of entropion at 24 months will be analysed by ordered logistic regression.

1. *Conjunctivilisation of the lid margin grade*

The effect of the intervention on the degree of conjunctivilisation at 24 months will be analysed by ordered logistic regression.

1. *Corneal opacification*
   1. Descriptive measures of the baseline severity of CO
   2. Description of the change in CO between baseline and one and two year follow up time-points.
   3. Ordinal logistic regression analysis for change in CO category at one year and two years respectively, to identify factors associated with it, such as inflammation.
   4. The effect of the intervention on the degree of change in CO between baseline and 24 months will be analysed by ordered logistic regression.
2. *Visual acuity*

The effect of the intervention on the visual acuity (logMAR score) at 12 and 24 months will be analysed by linear regression.

1. *Surgical complications and recurrence rate (in surgical arm)*

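### The letter-by-letter logMAR rule has the wrong sign: letters read beyond the last complete line raise the score when they should lower it

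*Protocol*

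**What the plan says.** Acuity scoring is set out in the protocol, Appendix B, Patient Examination, under Visual Acuity. The test uses an "EDTRS tumbling E logmar chart at 4m". The steps are:

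- Testing: "Test to lowest line on which any letter can be read. Complete whole line, even if many mistakes".
- Base score: "Take the LogMAR score for the lowest complete line read".
- Letter adjustment: "Add 0.02 x n to this score, where n = the number of letters read from the non-completed line".
- Distance adjustment: "If chart is read at 2m: add 0.3 correction" and "If chart is read at 1m: add 0.6 correction".

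The score is used in two places in the Analytical Plan for Trial 2. Acuity is among the baseline characteristics tabulated by arm, and it is a secondary outcome: "The effect of the intervention on the visual acuity (logMAR score) at 12 and 24 months will be analysed by linear regression".

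On timing, section B (Trial Follow-up Phase) lists visual acuity as its own aim at the one-year visit, next to the full examination. Under "Two year follow up" it lists a full examination with photography, and swabs, but does not name acuity.

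**The concern.** Two adjustments in one instruction point in opposite directions. Moving the chart nearer makes the task easier, and the score goes up to reflect poorer vision. Reading extra letters on a smaller line shows better vision, yet the score also goes up. Both cannot be right on one scale.

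At stake are the absolute acuity values at baseline and follow-up, the recorded direction of small changes in an individual eye, and the precision of the acuity analyses at 12 and 24 months. Acuity is a pre-specified secondary outcome, so its scoring formula should be correct before any acuity result is reported.

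**Working it through.** **Inputs.** From Appendix B: base score L is the lowest complete line; +0.02 per letter read on the non-completed line; +0.3 at 2 m; +0.6 at 1 m. Assumed, not stated: 5 letters per line and 0.1 logMAR per line (0.1 / 5 = 0.02, which matches the per-letter value), and only one part-read line, so that n runs from 0 to 4.

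**Step 1: direction of the scale, from the plan's own figures.** The correction for reading at distance d on a 4 m chart is log10(4/d).

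- 2 m: log10(4/2) = 0.301, stated as 0.3.
- 1 m: log10(4/1) = 0.602, stated as 0.6.

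Both reproduce. An easier, nearer test gives a higher score, so higher means worse.

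**Step 2: the letter rule against that scale.** The written rule gives L + 0.02n. On a scale where higher is worse it should be L - 0.02n. The error is (L + 0.02n) - (L - 0.02n) = 0.04n. With L = 0.50:

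| n | Written rule | Subtracting | Error |
|---|---|---|---|
| 0 | 0.50 | 0.50 | 0.00 |
| 1 | 0.52 | 0.48 | 0.04 |
| 2 | 0.54 | 0.46 | 0.08 |
| 3 | 0.56 | 0.44 | 0.12 |
| 4 | 0.58 | 0.42 | 0.16 |

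Reading the fifth letter completes the 0.40 line. The written score then falls from 0.58 to 0.40, a drop of 0.18 for a letter worth 0.02. If n is evenly spread over 0 to 4 (an assumption), the mean error is 0.04 x 2 = 0.08 and its SD is 0.04 x √2 = 0.057.

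**Step 3: can another reading rescue the rule?** Suppose the base were the last line attempted, here 0.40. Adding 0.02 would then be right for letters missed: 4 read and 1 missed gives 0.40 + 0.02 = 0.42. Adding it for letters read gives 0.40 + 0.08 = 0.48, which is still wrong. The text says letters read.

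**Step 4: how far the ranking is disturbed.** Take lines 0.0 to 1.0 with n = 0 to 4. That is 55 possible scores and 55 x 54 / 2 = 1485 pairs. All 11 x 10 = 110 same-line pairs are reversed. The other 1375 pairs, from different lines, keep their order, because the most that can be added (0.08) is less than one line step (0.10).

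**Step 5: effect on the comparison between arms.** The documents give no SD for acuity, so take 0.2, 0.3 and 0.5 as a range, with acuity normally distributed. The position within a line is then nearly unrelated to the true score, so the error variance adds: 0.04² x 2 = 0.0032.

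- SD 0.2: √(0.0400 + 0.0032) = 0.208, up about 4%.
- SD 0.3: √(0.0900 + 0.0032) = 0.305, up about 2%.
- SD 0.5: √(0.2500 + 0.0032) = 0.503, up about 0.6%.

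Simulation under the same assumptions gave these SDs, a correlation of 0.96 to 0.99 between written and correct scores, and true arm differences of 0, 0.05 and 0.10 recovered to within 0.0001.

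**Step 6: the schedule.** The one-year list names the full examination and visual acuity as two items. The two-year list names only the first of these. The analysis is planned for both time points. Appendix B, however, places Visual Acuity first within the Ophthalmic Examination, so a full examination may already include it.

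**The case against.** The strongest reply is that the error hardly touches what the trial will conclude. The same rule applies in both arms, so the average upward shift of about 0.08 cancels in the difference, and the loss of precision is small (step 5). Acuity is one of several secondary outcomes. The primary outcome is lashes touching the eye, so the sample size, the margin and the non-inferiority conclusion do not depend on this score. The baseline record form has fields for line, letters and distance, so correct scores can be derived from the raw entries. All of this stands. It limits the harm but does not make the instruction right.

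Three stronger readings are tempting, and the documents do not support them:

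- A reader might infer that the acuity scale is inverted and the randomised comparison wrong. The reversal is confined to scores on the same line, and the arm difference is nearly preserved.
- A reader might infer that every acuity value is wrong. The error is 0.04n, which is zero when n = 0.
- A reader might infer that the 24-month analysis will have no data. Because Appendix B puts acuity inside the examination and the two-year visit includes a full examination, the schedule is ambiguous; it does not show that acuity is omitted.

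**Conclusion.** The letter rule is wrong as written. This follows from the distance corrections in the same instruction, and nothing elsewhere in the text at hand corrects it. The direction of the error needs no outside assumption.

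Its size does. With 5 letters per line, 0.1 logMAR per line and one part-read line, individual scores are too high by 0 to 0.16 logMAR. The mean of 0.08 further assumes that n is evenly spread. Reported absolute acuity would look worse than it is, and a gain from 0 to 4 extra letters on one line (true change -0.08) would be recorded as +0.08.

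The limited effect on the comparison between arms rests on the assumed SDs, on normally distributed acuity and on the rule being applied alike in both arms. The point is a certain but contained error in a secondary outcome. The two-year listing is a separate, minor matter of wording.

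**What to change.** In Appendix B, replace the verb in the letter step so that 0.02 x n is subtracted from the score of the lowest complete line. An equivalent alternative is to take the last line attempted as the base and add 0.02 for each letter missed on it. Use one version only, and state the letters per line and the line step.

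Recalculate all acuity scores from the recorded line, letters and distance before any analysis. These fields can be confirmed on the baseline form; check that the follow-up forms hold them too.

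In section B, name visual acuity explicitly at the two-year visit, so that the schedule matches the planned 24-month analysis.

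The cost is one changed word, one added line in the schedule and a recalculation. Where the raw entries were kept, no new measurement is needed to correct the scores.
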